### Data collection

Baseline data collection will be integrated into the initial online health check questionnaire. This will include: year of birth, gender, occupational classification, height, weight, smoking status, dietary consumption of fruit and vegetables (portions per day), level of physical activity (minutes per week of vigorous, moderate and mild activity), frequency of consuming alcohol, average consumption on a drinking day, and frequency of drinking more than 6 drinks on one occasion (AUDIT-C), and health related quality of life (EQ-5D). Instruments for collecting data on hospital admissions will be those used in the SIPS and AESOPS trials of screening and brief intervention in multiple settings [29-31].

Follow-up data collection will be undertaken online. At follow-up participants will be asked to complete the TOT-AL, AUDIT, EQ-5D, report the number of days of sickness absence in the past 3 months and number and duration of any hospital admissions.

Data on numbers of health checks completed and proportion of employees scoring 5 or more on the AUDIT-C will be recorded. Use of DYD, including pages visited will be recorded using Google analytic software.

Data on costs of the intervention will be estimated from the costs incurred in the trial (separating out trial costs from intervention costs) for preparatory communications with stakeholders, preparing the invitations, developing the online health check, developing the tailored feedback, applying the software to provide tailored feedback, and updating.

Follow-up rates will be maximised by sending up to three e-mail requests for data. Non-responders will be contacted by post and phone to see if they received the e-mail reminders and request online completion. Participants who do not respond to these requests will be sent a final email and / or phoned asking just for primary outcome data (amount of alcohol consumed in past 7 days).

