### Analyses

Analyses will compare outcomes between groups at three months following the intention to treat principle. The principal analysis will be conducted using a generalised linear model with identity link and Gaussian error. The baseline AUDIT-C score will be included as a patient level explanatory variable, along with a classification variable for workplace and for randomised group. Analogous models will be conducted for secondary outcomes. We will conduct an additional prognostic model examining subject and organisational factors (and potential interactions) associated with the size of any treatment effect. For the economic evaluation we will design a decision analytical model in line with National Institute of Health and Clinical Excellence (NICE) guidance to determine the incremental cost per quality adjusted life year (QALY) gained, calculated using the EQ-5D, and cost per reduction in units of alcohol consumed of the web-based screening and brief intervention compared to web-based screening alone at 3 months, 12 months and 10 years. As participants in the control group will be referred to DYD at 3 months, the 12 month analysis for the control group will assume that the costs and outcomes for the first 3 months of the trial would have continued for the next 9 months had they not received the intervention at 3 months. Effectively, costs and outcomes over 12 months for the control group will be cost and outcomes for the first 3 months multiplied by 4. Published data will be used for the 10 year model and all costs and outcomes will be discounted in accordance with NICE guidance. The primary cost- effectiveness analysis will be from the perspective of the NHS with a secondary cost-offset analysis from the perspective of the employer. Costs to the NHS will include the costs of hospital admissions. Unit costs will be taken from standard published sources such as Personal Social Services Research Unit (PSSRU) [32]. The cost to the employer will include the cost of implementing web based screening and brief intervention and the cost of the time it takes employees to complete web based screening and brief intervention. This will be offset by any cost savings associated with reduced number of days of sick leave for the screening and brief intervention group compared to the screening only group. We are aware of the potential seasonal variation in sickness absence and will address this in the sensitivity analyses. Analyses will be subject to deterministic and probabilistic sensitivity analyses. Modelling will be used to explore the relative cost-effectiveness of primary care versus work-place SBI.

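### The employer cost-offset analysis charges for screening plus intervention but credits only the saving over screening alone, so as worded it overstates net cost by the shared screening cost

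*Protocol article*

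**What the plan says.** The Analyses section defines the economic comparison as "web-based screening and brief intervention compared to web-based screening alone at 3 months, 12 months and 10 years". The main measure is the "incremental cost per quality adjusted life year (QALY) gained, calculated using the EQ-5D". On perspective it says: "The primary cost- effectiveness analysis will be from the perspective of the NHS". The one NHS cost it names is in the sentence "Costs to the NHS will include the costs of hospital admissions".

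A secondary cost-offset analysis takes the employer's perspective. Its cost side has two items. The first is delivery: "The cost to the employer will include the cost of implementing web based screening and brief intervention". The second is staff time: "the cost of the time it takes employees to complete web based screening and brief intervention". Its saving side is the "reduced number of days of sick leave for the screening and brief intervention group compared to the screening only group".

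The Data collection section says that intervention costs will be estimated from trial expenditure, with trial costs separated out. The items listed include "preparing the invitations, developing the online health check, developing the tailored feedback". The section on intervention and comparator conditions has every consenting employee complete the health check, and gives both arms the same tailored feedback on BMI, smoking, diet and physical activity. Until follow-up is complete, the arms differ only in the alcohol feedback and advice and the referral to DYD.

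**The concern.** A cost-offset is interpretable only if costs and savings are measured against the same alternative. Here the cost side is the whole cost of screening plus intervention, which is the cost relative to having no programme. The saving side is relative to screening alone. The cost of the health check, and of the time employees spend on it, is incurred in both arms, yet as worded it is set against a saving from which any effect of screening has already been removed.

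The aims cover cost-effectiveness and the costs and benefits of offering the programme through the workplace. An employer reading the result could conclude that adding the alcohol component loses money when the like-for-like comparison shows a saving.

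A lesser question arises for the primary NHS analysis. It names no delivery cost, and the article assigns that cost to the employer, so a reader needs to know what the NHS cost per QALY does and does not cover.

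**Working it through.** The article states no unit cost, QALY gain or sick-leave saving, so there is no figure to reproduce. The check is algebra on the items it names.

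**Per-head quantities**
- S: cost common to both arms (invitation, health check, non-alcohol feedback, employee time on these).
- B: added cost of alcohol feedback and DYD, including employee time on them.
- V: value of the sick-leave reduction against screening only.
- dH: difference in NHS admission cost. dQ: difference in QALYs.

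**Which items are shared.** Invitations and the health check serve both arms. Tailored feedback and its software are shared except for the alcohol component. The Data collection section separates trial costs from intervention costs, but does not separate shared costs from those that differ between arms.

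**Employer analysis**
- As worded: (S + B) − V.
- Difference between arms: (S + B) − S − V = B − V.
- Overstatement: [(S + B) − V] − (B − V) = S, whatever the values.
- The sign changes when B < V < S + B.

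Illustration in pounds per head. Every input is an assumption:

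| S | B | V | As worded | Like for like |
|---|---|---|---|---|
| 5 | 1 | 5 | +1 | −4 |
| 5 | 1 | 25 | −19 | −24 |
| 5 | 10 | 5 | +10 | +5 |
| 5 | 10 | 25 | −10 | −15 |
| 20 | 1 | 5 | +16 | −4 |
| 20 | 1 | 25 | −4 | −24 |
| 20 | 10 | 5 | +25 | +5 |
| 20 | 10 | 25 | +5 | −15 |

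In three of the eight rows (the first, fifth and last) a net cost becomes a net saving.

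**NHS analysis**
- Ratio from the named item only: dH/dQ.
- Ratio with incremental delivery cost: (dH + B)/dQ.
- Difference: B/dQ.

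With assumed B of £1 to £50 and dQ of 0.001 to 0.005, the difference runs from 1/0.005 = £200 to 50/0.001 = £50,000 per QALY. That 250-fold range reflects only the assumptions. It shows that B could matter, not that it does.

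**The case against.** **Employer analysis.** The article uses the phrase for screening and brief intervention as the name of an arm, so listing what that arm costs need not mean that the comparator's screening cost is left in. The overall comparison is defined as incremental, and a full health-economics plan may net out common costs. Gross programme cost also matters to an employer, which cannot deliver the alcohol feedback without the screen.

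Part of this stands: the overstatement follows from the wording and would disappear if netting were done. But the article states what is charged and what is credited, the two sides use different comparators, and no netting step is given. Gross cost is a fair question, but it would need a saving measured against no programme, and the trial has no such arm.

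**NHS analysis.** A reader might infer that the primary ratio leaves out intervention cost and is therefore biased in favour of the intervention. The article does not support this. The word used is include, which is not exhaustive. The Outcomes section lists implementation costs and resources for the economic evaluation as a whole. If the employer pays, leaving that cost out follows from the NHS perspective. Requiring it in the primary numerator whoever pays would replace the chosen perspective with a debatable one.

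A reader might also infer that two ratios are wrong, or that neither analysis compares the randomised arms incrementally. The employer result is a net cost, not a ratio, and the primary measure is explicitly incremental against screening alone.

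**Conclusion.** The point holds for the secondary employer analysis. Followed literally, it overstates the employer's net cost by S, the screening cost that both arms incur, and this could reverse the conclusion. The direction and the algebra rest only on both arms receiving the health check, which the article states, and on no unstated netting step. The size cannot be computed from the document, and the pound values above are illustrations.

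For the primary NHS analysis there is no error, only a limit on interpretation. If the implementation cost stays with the employer, the ratio describes consequences for the NHS budget and not the full cost of obtaining the QALYs. This matters most for the planned modelling of primary care against workplace delivery. If primary care delivery is costed to the NHS (an assumption, as the article does not say) while workplace delivery is not, part of any advantage for the workplace would come from who pays.

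**What to change.** 1. **Employer analysis.** Charge only costs that differ between arms: alcohol feedback, DYD and employee time on them. Equivalently, enter health-check and shared feedback costs in both arms so that they cancel. Keep the sick-leave saving against screening only. Report total programme cost separately, as a description for employers considering the whole package.
2. **Cost collection.** Tag each implementation item as shared or alcohol-specific when it is recorded, and split the tailored-feedback and software items accordingly.
3. **NHS analysis.** Keep the NHS perspective as primary, state who is assumed to pay for delivery, and add a sensitivity analysis with B in the numerator. Show the comparison of primary care with workplace delivery both ways.

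The cost is some rewording and slightly more tabulation of costs that are already to be collected. The randomised design and the primary economic perspective do not change.

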
## Discussion

The design of the trial raises some interesting methodological and ethical issues, discussed here.

### Comparator and duration of follow-up

The trial uses a wait list design, with the comparator group receiving no feedback on their alcohol consumption until they have completed data collection at the primary outcome point (3 months). We consider this is ethical as a) this is a non-help seeking population; b) the time-course of alcohol misuse is long (many years) and it is unlikely that three months delay in provision of feedback and advice is likely materially to alter outcomes; and c) all participants are advised to consult their GP if they have any concerns about their health. We had initially considered a 12 month primary outcome point but decided this was potentially unethical as 12 months delay could potentially be harmful. Moreover, our procedures had to be acceptable to the collaborating workplace, which had indicated that a three month follow-up period was the longest they would consider acceptable. Our previous work had suggested that reductions in alcohol consumption seen at 3 months were maintained at 12 months [33], although the data from that trial may not apply to the different population recruited here.

### Dependent drinkers

A very small proportion of participants are likely to be dependent drinkers. NHS Information Centre statistics for 2007 report the prevalence of moderate or severe dependence as 1% in men and 0% in women in the general adult population. An additional 8.3% of men and 3.6% of women have mild dependence. People with moderate or severe dependency require detoxification under medical supervision, but those with mild dependence do not. We are not assessing level of dependency, and will not be able to identify participants who are moderately or severely dependent on alcohol. Down Your Drink provides information to users about dependency, including warnings not to stop consumption suddenly and advice to seek medical help.

### Baseline data collection

Collecting baseline data on alcohol consumption would increase the power of the study, as it would allow for determination of individual change. However, alcohol consumption is notoriously sensitive to assessment, with simple measurement of past week alcohol consumption or completion of the Alcohol Use Disorders Identification Test (AUDIT) resulting in a decrease in consumption of about 20% [34]. This reactivity of assessment is thought to be a contributing factor to the lack of difference seen in many alcohol trials [35] and for this reason, we decided against collecting baseline data on alcohol consumption.

### Advantages and disadvantages of online trials

Advantages of conducting trials on-line compared to conventional trial methods include rapid and easy recruitment, automated randomisation with concealment of allocation, and automated data collection [36]. For example, our on-line trial of DYD recruited nearly 8,000 participants over 2 years with no advertising and no marginal cost per additional participant recruited [33]. Automated data collection, whereby participants are automatically sent e-mails requesting follow-up data with embedded hyperlinks in the e-mail, allowing participants to access questionnaires with one click, is relatively cheap, and because participants enter data online, it can be automatically transferred to the trial database, obviating the need for manual data entry and preventing transcription errors. Thus large trials can be undertaken at relatively low cost. There are disadvantages to conducting trials on-line, including difficulty in describing the population from which the sample was drawn and knowing what proportion of potential participants actually participated (affecting external validity), and low follow-up rates (affecting internal validity). Low follow-up rates are probably related to the relatively impersonal nature of on-line trials and the ease with which e-mail reminders can be ignored or deleted. This proposal capitalises on the advantages of on-line trials while avoiding the disadvantages. Recruiting from a work-force ensures we know the total number of employees contacted, and also allows us to use multiple forms of follow-up, including telephone and post, thus improving retention.

## Abbreviations

AUDIT: Alcohol use disorders identification test; AUDIT-C: Three item screening test derived from the AUDIT; BMI: Body mass index; DYD: Down your drink; NICE: National Institute of Health and Clinical Excellence; NHS: National health service; PSSRU: Personal social services research unit; QALY: Quality adjusted life year; SBI: Screening and brief intervention; TOT-AL: Total past week alcohol consumption – an online measure of past week alcohol consumption; UK: United Kingdom; WHO: World health organisation.
